## Abstract

**Background::**

Fulminant myocarditis has a sudden onset and rapid progress, which can easily cause multiple organ failure. Acute kidney injury is a common complication. ECMO (extracorporeal membrane oxygenation) and CRRT (continuous renal replacement therapy) have been used in the treatment of fulminant myocarditis, but the combination of the 2 has an impact on the prognosis. There is still a big controversy. Therefore, the purpose of this randomized controlled trial is to evaluate the nursing effect and long-term efficacy and safety of ECMO combined with CRRT in the treatment of fulminant myocarditis.

**Methods::**

This is a prospective randomized controlled trial to study the effectiveness and safety of ECMO combined with CRRT in the treatment of fulminant myocarditis. Approved by the clinical research ethics committee of our hospital. Patients were randomly assigned to 1 of 2 treatment options:

Observation indicators include: basic vital signs, laboratory indicators, echocardiographic changes, complications, and outcomes. SPSS 25.0 (Chicago, IL) version statistical software package was used to analyze the data.

**Discussion::**

This study will evaluate the nursing effect and long-term efficacy and safety of ECMO combined with CRRT in the treatment of fulminant myocarditis. The results of this experiment will provide clinical evidence for the treatment of fulminant myocarditis with ECMO and CRRT.

**Ethics and dissemination::**

Private information from individuals will not be published. This systematic review also does not involve endangering participant rights. Ethical approval was not required. The results may be published in a peer-reviewed journal or disseminated at relevant conferences.

**OSF Registration number::**

DOI 10.17605/OSF.IO/PAQBZ.

## Introduction

1

Fulminant myocarditis is a systemic disease dominated by myocardial inflammatory damage caused by infections, autoimmune diseases, etc. Patients can quickly develop severe hemodynamic disturbances, heart failure, and severe malignant arrhythmia, leading to multiple organs such as liver and kidney dysfunction, the early mortality rate is extremely high.^[1,2]^ Early adoption of “A life support-based comprehensive treatment regimen” including mechanical life support, immunomodulatory therapy, antiviral therapy (especially neuraminidase inhibitors), reduce the hospital mortality rate of FM patients.^[3]^

Extracorporeal membrane oxygenation (ECMO) takes the venous blood in the body out of the body and injects it into the patient's arteries or veins through a special material artificial heart-lung bypass oxygenation device, which plays a role of partial heart-lung replacement.^[4]^ It is believed that ECMO can be used as a first-line treatment option for fulminant myocarditis.^[5]^ Fulminant myocarditis often causes renal hypoperfusion, and in ECMO circulation support, hemolysis caused by red blood cell destruction can cause acute kidney injury (AKI), which seriously affects the prognosis of patients.^[6]^ Studies have shown that AKI and overload fluid occur in 70% to 85% of ECMO patients.^[7]^ Continuous renal replacement therapy (CRRT) is an extracorporeal blood purification therapy that can replace impaired renal function for a long time. It removes toxins and cytokines through diffusion and convection methods, and reduces cardiac load through ultrafiltration Maintaining hemodynamic stability well.

The impact of ECMO combined with CRRT on the prognosis is still controversial. Studies have pointed out that regardless of whether AKI occurs, and whether CRRT is performed, the difference in mortality of CF patients in the intensive care unit is not statistically significant.^[8]^ Therefore, this research program will study the effectiveness and safety of ECMO combined with CRRT in the treatment of fulminant myocarditis through randomized controlled trials.

## Materials and methods

2

### Study design

2.1

This is a prospective randomized controlled trial to study the effectiveness and safety of ECMO combined with CRRT in the treatment of fulminant myocarditis. We followed the Consolidated Standards of Reporting Trials (CONSORT) guidelines for reporting randomized trials and provided a CONSORT flow diagram (Fig. 1) and the Standard Protocol Items: Recommendations for Interventional Trials (SPIRIT) 2013 statement.

**Figure 1 F1:**
[figure not shown]
Flow diagram.

### Ethics and registration

2.2

This research program is in accordance with the Helsinki Declaration and approved by the Clinical Research Ethics Committee of our hospital. This protocol has been registered in open Science Framework (OSF)(Registration number: DOI 10.17605/OSF.IO/PAQBZ). All patients need to sign a written informed consent before they are randomly assigned to continue the trial.

### Sample size

2.3

In order to draw reliable conclusions, this study will include as many qualified samples as possible, referring to similar studies,^[8]^ we set the minimum number of people in each group of studies to 40, and the final number will be based on actual recruitment.

### Patients

2.4

Inclusion criteria: ①Meet the diagnostic criteria for fulminant myocarditis of the European Heart Collaboration Group;^[9]^②No previous serious underlying heart disease; ③A viral infection of the respiratory system occurred before the onset; ④After the onset, the condition deteriorated rapidly, the left heart function was severely impaired, the hemodynamics was unstable, and circulatory and respiratory support was needed; ⑤Be over 18 years old.

Exclusion criteria: ①Those who use ECMO for other reasons; ②;Severe irreversible multiple organ damage; ③Pregnant women with severe heart failure; ④Patients with congenital and acquired diseases that cannot be corrected after cardiac surgery; ⑤Cardiopulmonary Resuscitation (CPR) for more than 30 minutes; ⑥Thouse who are unable to understand the research plan after explanation or unwilling to participate.

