
The treatment group adopts the combined treatment mode of ECMO and CRRT, and the control group adopts the ECMO treatment mode. Any emergencies during treatment will be dealt with according to the expert consensus opinion of fulminant myocarditis.^[9,13]^ All nurses and doctors involved in the treatment are experienced professionals.

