## Discussion

3

Patients with fulminant myocarditis progress rapidly and are often accompanied by difficult to correct hemodynamic disturbances or stubborn fatal arrhythmias. Therefore, the early use of effective mechanical assist devices is the key to improving the prognosis of such patients.^[3,15]^ It has been reported in the literature that the survival rate of mechanical assist devices for fulminant myocarditis is 57% to 80%.^[3,16]^ Early and timely ECMO placement to maintain effective circulatory perfusion is the key to reducing the mortality of FM. However, for long-term use of ECMO treatment, it should be noted that the probability of complications of ECMO treatment such as limb ischemia, abnormal coagulation function, bleeding, and infection will be greatly increased.^[17]^ Some researchers believe that ECMO combined with CRRT avoids the risk of bleeding at the puncture site during ECMO-assisted systemic anticoagulation. At the same time, it can measure the pressure of the ECMO membrane before and after the membrane, reduce the pressure measurement device, and reduce the risk of infection.^[18]^ Studies have shown that during EMCO treatment, about 50% of patients may be combined with CRRT treatment,^[19]^ which may be related to ECMO oxygenated blood flowing backward through the renal artery, ECMO-related inflammation activation, high anticoagulation state, hemolysis, etc. These factors are related.^[20]^ The integrated use of ECMO and CRRT in parallel can achieve joint support of multiple organs such as heart, kidney, and lung in 1 cardiopulmonary bypass pathway. However, some scholars believe that the use of CRRT during ECMO may increase the risk of in-hospital mortality.^[21]^ Therefore, whether the early application of CRRT is beneficial to the prognosis of patients with fulminant myocarditis still needs clinical research to verify.

This study also has the following limitations: the sample size included in this study is limited, which may affect the results. The planned follow-up time for this study is short, and there is no assessment of the long-term efficacy and safety of the treatment plan. If necessary, we will extend the follow-up time and pay more attention to its long-term efficacy.

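### Section 2.4 has no renal entry criterion, so a patient already on, or already needing, renal replacement can be randomised to ECMO without CRRT

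*Protocol article*

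**What the plan says.** Section 2.4 (Patients) gives a complete numbered list of five inclusion and six exclusion criteria. The organ-function terms for entry are cardiac, circulatory and respiratory. No criterion mentions kidney function, AKI, dialysis, current renal replacement or an indication for it. The only exclusion for organ damage in general is "Severe irreversible multiple organ damage".

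Section 2.6 (Interventions) gives the treatment group ECMO with CRRT, while "the control group adopts the ECMO treatment mode". It adds that "Any emergencies during treatment will be dealt with according to the expert consensus opinion of fulminant myocarditis". The content of that consensus is not reproduced.

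The Introduction describes renal involvement as part of the disease: "Fulminant myocarditis often causes renal hypoperfusion", and the illness progresses quickly, "leading to multiple organs such as liver and kidney dysfunction". It also reports that "AKI and overload fluid occur in 70% to 85% of ECMO patients". The Discussion says that during ECMO "about 50% of patients may be combined with CRRT treatment".

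**The concern.** CRRT is the only treatment that differs between the arms, so whether a patient already needs renal replacement at entry decides whether random allocation to no CRRT is reasonable. Whether early CRRT helps is an open question for a patient without an established need. For a patient already on dialysis, or already judged to need renal replacement, the control assignment lacks equipoise.

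For such a control there are two outcomes, and they are alternatives whose effects should not be added together:

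- CRRT is withheld. The contrast between the arms stays intact, but an indicated therapy is denied.
- CRRT is given. The patient is safe but is a control in name only, and the difference between the arms is diluted in proportion to the share affected.

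**Working it through.** **Reading the criteria.** Two kinds of patient were set against the exclusion for "Severe irreversible multiple organ damage", which needs damage that is severe, irreversible and in multiple organs.

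| Patient at entry | Irreversible? | Multiple organs? | Excluded? |
|---|---|---|---|
| Chronic dialysis for isolated kidney failure | yes | no | no |
| Reversible AKI, already on or judged to need renal replacement | no | not necessarily | no |

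None of the other five exclusions refers to the kidney. Both patients can therefore be randomised if they otherwise qualify. The consensus clause in section 2.6 applies to emergencies during treatment and does not bar entry.

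**Inputs for the size.**

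- 40 per group, the minimum in section 2.3. The article gives no rates, effect or power behind this number, so there is no plan figure to reproduce.
- Two-sided 5% test (section 2.9).
- Share x of patients with established need at entry: not given. Assumed 5%, 10% and 25%. The 50% CRRT use and the 70% to 85% AKI or fluid overload describe the ECMO course as a whole, so they are at most loose upper limits for x.
- Control mortality: cited survival with mechanical assist devices is 57% to 80% (Discussion), so mortality is 20% to 43%, with midpoint (20 + 43)/2 = 31.5%. Both 31.5% and 43% are used.
- True mortality reduction of 20 points: an assumption.

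**Controls affected.** The expected number is 40x:

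- 40 × 0.05 = 2
- 40 × 0.10 = 4
- 40 × 0.25 = 10

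The chance of at least one affected control at x = 5% is 1 − 0.95^40 = 0.871.

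**If CRRT is withheld.** These are the numbers denied an indicated therapy, and there is no dilution.

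**If CRRT is given.** Assume these controls take the full 20-point benefit. Control mortality becomes p_c − 0.20x, and the observed difference is 0.20(1 − x), which is 19, 18 or 15 points. Power for two proportions with pooled variance under the null is

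Φ( [ d√n − 1.96·√(2·p̄(1 − p̄)) ] / √( p₁(1 − p₁) + p₂(1 − p₂) ) ),

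where n = 40, d = p₁ − p₂ and p̄ = (p₁ + p₂)/2.

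Worked case, 31.5% vs 11.5%: d√n = 0.20 × 6.325 = 1.265; p̄ = 0.215, so 1.96 × √0.3376 = 1.139; the denominator is √(0.2158 + 0.1018) = 0.5635. Then Φ(0.126/0.5635) = Φ(0.224) = 0.589.

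| x | Control vs treated | Power | Control vs treated | Power |
|---|---|---|---|---|
| 0 | 31.5% vs 11.5% | 0.589 | 43% vs 23% | 0.476 |
| 5% | 30.5% vs 11.5% | 0.552 | 42% vs 23% | 0.441 |
| 10% | 29.5% vs 11.5% | 0.514 | 41% vs 23% | 0.406 |
| 25% | 26.5% vs 11.5% | 0.399 | 38% vs 23% | 0.305 |

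**The case against.** The strongest reply is that need at entry may be rare. The Discussion links CRRT use largely to ECMO itself (retrograde flow, inflammation, anticoagulation, haemolysis), and renal hypoperfusion or kidney dysfunction before ECMO is not yet an indication for renal replacement. This stands: the frequency at randomisation cannot be derived from the article, and the 25% scenario has no direct support.

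The power figures also rest on several assumptions. The survival range is for mechanical assist devices generally. The dilution model credits CRRT with a full benefit, although the article itself calls the effect disputed and mentions a possible increase in in-hospital mortality. This stands too, so the figures are illustration only. At 5% to 10% the loss is about 4 to 8 points, from a starting power of only 48% to 59%.

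Nothing in the article forbids CRRT in controls, and the consensus may allow it. That is possible, but withholding cannot be ruled out either. If the consensus does allow CRRT, the problem changes from denied therapy to crossover; it does not disappear.

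Finally, an entry exclusion does nothing for need that arises after randomisation, which is probably the larger part. That is correct and limits what the fix achieves. It is no reason to enrol patients whose need is already known.

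**Conclusion.** The concern holds. The eligibility list is stated in full, and followed as written it admits patients for whom ECMO without CRRT is not an acceptable random assignment. It should be fixed, chiefly for safety and equipoise. Even at an assumed 5% entry share, about two of 40 controls would be denied indicated therapy or would cross over, with an 87% chance of at least one. The loss of power is secondary: about 4 points at 5%, 7 to 8 points at 10%, and 17 to 19 points at 25%. It arises only if CRRT is given to those controls, and it depends on the assumed share, the 20-point effect and full benefit in crossovers.

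**What to change.** Add one exclusion to section 2.4: *receiving any form of renal replacement therapy, or with renal replacement already judged necessary by the treating team, at the time of randomisation*. Patients with AKI but no established need stay eligible, so the population in the rationale is kept. The judgement clause has no objective threshold and could be applied differently by different clinicians.

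Optionally, adjust the outcome comparison for baseline renal function. Sections 2.7 and 2.8 already have kidney function recorded before treatment, so no new data are needed. The randomisation scheme need not change.

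The cost is one sentence and a protocol amendment, somewhat slower recruitment and a slightly narrower target population. To randomise 80 patients, 80/(1 − x) otherwise eligible patients are needed: 84.2, 88.9 or 106.7 at x = 5%, 10% or 25%, which is about 85, 89 or 107. CRRT need that arises after entry is not addressed by this change.

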### Study design

2.5

Eligible participants were randomly assigned to the treatment group or the control group at a ratio of 1:1 using a random tool based on the central network. Randomization was performed without any stratification generated by an independent statistician who was not involved in trial implementation or statistical analysis using SAS 9.3 software (SAS Institute, Cary, NC). The clinical research coordinator entered the participant information on the tablet, and was given a random number. The research assistant gets the participant's assignment from the computer. Throughout the research process, the research assistant is responsible for screening, recruiting participants, and assigning random numbers to the included participants. The result assessor is responsible for the assessment of the scale.

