### Statistical analysis

2.9

The SPSS 25.0 software was used for statistical analysis. Measurement data are expressed as mean ± standard deviation or median (quartile), and count data are expressed as number of cases. The independent sample *t* test or Mann–Whitney *U* test was used for the comparison of measurement data, the paired *t* test was used for the comparison within the group, and the Chi-Squared test or Fisher exact probability method was used for the comparison of count data. All are two-sided tests, with *P* < .05 as the difference is statistically significant.

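### Unstratified allocation with only unadjusted tests leaves kidney injury at entry to chance: the design is valid, but adjusting for it is a cheap, small improvement

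*Protocol article*

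**What the plan says.** - **Allocation (Protocol article, section 2.5).** Patients are "randomly assigned to the treatment group or the control group at a ratio of 1:1" through a central network tool. On stratification the text reads "Randomization was performed without any stratification generated by an independent statistician". No reason is given.
- **Size (section 2.3).** "we set the minimum number of people in each group of studies to 40", and "the final number will be based on actual recruitment". Forty per arm is therefore a floor, and no total is fixed.
- **Analysis (section 2.9).** For binary outcomes, "the Chi-Squared test or Fisher exact probability method was used for the comparison of count data"; for measurements, a t test or Mann-Whitney test. None is adjusted for a baseline factor. "All are two-sided tests", with significance at P "< .05 as the difference is statistically significant".
- **AKI (Introduction).** Low renal perfusion and haemolysis during ECMO "can cause acute kidney injury (AKI), which seriously affects the prognosis of patients". The same section then cites a study in which intensive-care mortality did not differ significantly by AKI or by use of CRRT.
- **Eligibility (section 2.4).** There is no renal criterion, so patients with and without AKI are eligible.
- **Baseline data (sections 2.7 and 2.8).** Kidney function is a listed indicator, and the indicators are recorded before treatment.

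**The concern.** CRRT replaces renal function, so renal status at entry is the obvious candidate for a baseline factor that influences outcome in this trial. As the article stands, nothing protects its balance at allocation and none of the named tests accounts for it. In a trial of about the minimum size, the arms could differ visibly in AKI at entry. Readers would then doubt the comparison, and the unadjusted tests would use the data less efficiently than they could. What is at stake is precision and how far the one realised result is believed, not the validity of the randomisation.

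**Working it through.** **Inputs from the article.** 40 per arm (section 2.3, minimum); 1:1 allocation without stratification (2.5); unadjusted tests, two-sided 0.05 (2.9); survival on mechanical support 57% to 80% (Discussion), so mortality 20% to 43%, midpoint 31.5%.

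**Assumed.** The article gives no AKI prevalence at entry. Its 70% to 85% is for AKI and fluid overload occurring in ECMO patients, so 50%, 70% and 85% are used as a range. It gives no mortality by AKI status either; the scenarios are listed in step 3.

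The figure of 40 cannot be reproduced, because no effect size, event rate or power is stated with it.

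**1. Chance imbalance.** The AKI counts in the two arms are taken as independent Binomial(40, p). The standard deviation of the difference in proportions is sqrt(2p(1 − p)/40), for example sqrt(2 × 0.5 × 0.5/40) = 0.112 at p = 0.50. The exact probabilities are:

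| Prevalence p | SD of difference | ≥10 points (≥4 patients) | ≥15 points (≥6) | ≥20 points (≥8) |
|---|---|---|---|---|
| 50% | 0.112 | 43% | 22% | 9% |
| 70% | 0.102 | 39% | 18% | 7% |
| 85% | 0.080 | 27% | 8% | 2% |

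These count both directions. They shrink if more than 40 per arm are recruited.

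**2. Effect on the mortality comparison.** Shift = imbalance × risk difference between patients with and without AKI.

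- 15-point imbalance: 0.15 × 0.20 = 3 points to 0.15 × 0.40 = 6 points.
- 20-point imbalance: 0.20 × 0.20 = 4 points to 0.20 × 0.40 = 8 points.
- Standard error of the difference at 31.5% mortality: sqrt(2 × 0.315 × 0.685/40) = 0.104, about 10 points.

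The shift stays below one standard error throughout.

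**3. Error rate and power.** Simulation of 400,000 trials with 40 per arm at two-sided 0.05. The unadjusted test is the chi-square test without continuity correction; the adjusted test is CMH by AKI. Power is for an assumed halving of mortality. Each cell gives type I error / power.

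| AKI prevalence; mortality without/with AKI | Unstratified, unadjusted | Stratified, unadjusted | Unstratified, CMH | Stratified, CMH |
|---|---|---|---|---|
| 50%; 20%/40% | 0.048 / 36.5% | 0.044 / 36.2% | 0.050 / 36.9% | 0.049 / 37.3% |
| 70%; 15%/40% | 0.048 / 39.9% | 0.041 / 39.4% | 0.050 / 40.7% | 0.049 / 40.8% |
| 70%; 10%/50% | 0.051 / 47.1% | 0.035 / 46.5% | 0.049 / 51.0% | 0.051 / 50.8% |
| 85%; 10%/40% | 0.049 / 43.9% | 0.043 / 43.5% | 0.050 / 44.8% | 0.048 / 45.0% |

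- The plan as written keeps its 5% level.
- Stratifying without adjusting makes the test conservative and does not raise power.
- Adjusting gains about 1 point or less in three scenarios and about 4 points (47.1% to 51.0%) where AKI raises mortality from 10% to 50%. Adding stratification to adjustment changes little.
- Only among trials with an imbalance of at least 20 points does the unadjusted type I error rise, to 0.067 to 0.119 across the scenarios.

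**The case against.** The strongest reply is that nothing here is wrong. Central 1:1 randomisation from an independent statistician's list is unbiased without stratification, and chance imbalance is already part of the 5% error rate. This stands, and it limits the point to efficiency and credibility. An adjusted analysis could also sit in an analysis plan that is not shown. That stands for adjustment, but not for stratification, which the article itself rules out.

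Several stronger readings are tempting, and the article does not support them:

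- **That imbalance would create or hide an effect.** This is true only conditionally on a large imbalance. Over all randomisations the planned test holds its level.
- **That AKI decides which control patients receive CRRT.** Section 2.6 gives the control arm ECMO and refers emergencies to an expert consensus. No rule on CRRT for controls is stated, and stratification would not settle that question.
- **That AKI certainly worsens outcome here.** The Introduction points both ways, and part of the AKI that it describes arises during ECMO. AKI that arises after randomisation cannot be stratified on.
- **That the minimum of 40 per group would usually be missed.** This presumes simple allocation and a fixed total of 80. Section 2.3 fixes no total, and an article may leave blocking to the full protocol.
- **That stratification was left out on purpose.** The text gives no reason, so no motive can be inferred.

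**Conclusion.** The point holds as a minor design-efficiency remark. Allocation ignores AKI and the named tests do not adjust for it, in a trial whose own rationale rests on renal function. At the minimum size, an AKI imbalance of at least 15 points would be seen in about 8% to 22% of trials. The randomisation and the planned tests remain valid, with overall type I error about 0.05. What is lost is at most about 4 power points, and about 1 or less in most scenarios tried, together with some credibility if a visible imbalance occurs. All of this rests on assumed AKI prevalence at entry, assumed mortality by AKI status, an assumed halving of mortality and exactly 40 per arm. With more patients the imbalance shrinks, and if AKI is not prognostic there is nothing to gain.

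**What to change.** 1. **Adjust the comparison.** State in section 2.9 that the arms are compared with adjustment for AKI or renal function at entry: for example, CMH by AKI yes/no for binary outcomes, and a model with the baseline renal value for measurements. This needs no new data, because kidney function is recorded before treatment, and it can still be done if recruitment has started, provided that it is fixed before the outcomes are seen.
2. **If recruitment has not begun, also stratify** allocation by AKI yes/no in the existing central tool. Two strata are few enough for about 80 patients. This should not be done without step 1, since stratification alone gains nothing.

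The cost of stratifying is a new list from the same statistician and one entry field. AKI yes/no also needs a definition fixed before allocation and usable in an emergency, which the article does not now give. Adjustment keeps the type I error at about 0.05 and loses essentially nothing if AKI turns out not to be prognostic.
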